## Outcome measurements and instruments

3

This study will use both self-assessment and other-assessment scales, and the study assessments will be completed partly by the patients online in self-help and partly with the help of an assessor. Analyses of these scales will be conducted by a statistician without knowing how the patient groups will be assigned.

The efficacy evaluation indicators include (1) Main indicators:

Between-group comparison of ISI scores between the two groups after intervention and within-group comparisons before and after the intervention.

The ISI is a brief sleep self-assessment tool with 7 items to evaluate the severity of a patient’s insomnia (38). Using a single-item scale from 0 to 3, it is primarily used to evaluate the severity of insomnia in patients. The ISI is highly sensitive, valid, reliable, brief, easy to administer, statistically easy to use, provides relevant information for diagnosis and treatment, and is a reliable tool for quantifying the perceived severity of insomnia. The intervention will be considered successful when, after 35 days, a significant difference in the ISI scores between groups is found in the study group compared to the control group. Also, within-group comparisons between the two groups before and after the intervention will be explored thereby confirming the effect of the intervention more clearly.

(2) Secondary indicators:

a. Between-group comparison of the total HAMA score reduction rate in the two groups of patients;

b. Between-group comparison of the HAMD total score reduction rate in the two groups of patients;

The HAMA (39)and HAMD (40, 41) are scales that measure the severity of anxiety and depressive symptoms and are considered to be among the most widely used scales with good reliability and validity in the measurement of anxiety and depression. The HAMA contains 14 items and the HAMD contains 17 items, most of which are scored on a 4-point scale (from 0 to 4).

c. between-group comparison of sleep latency reduction time before and after intervention in the two groups of patients;

d. intergroup comparison of the time of increase in total sleep duration before and after intervention in the two groups of patients;

e. Comparison between the two groups of patients before and after the intervention of the Pittsburgh Sleep Quality Index (PSQI) total score reduction rate and the change of each factor score;

(3) Other psychological scales:

The PSQI is a standardized self-administered questionnaire developed by Buysse et al. (1989), is one of the most widely used standardized scales for assessing the subjective quality of sleep (42). It consists of 19 self-assessment and 5 other-assessment entries, each calculated on a scale of 0 to 3, with “0” referring to no difficulty, “1” referring to mild difficulty, “2” referring to moderate difficulty, and “3” referring to severe difficulty, and the cumulative scores for each factor are the total score of the PSQI, which ranges from 0 to 21, with the higher scores indicating poorer quality of sleep, and ≥8 suggesting the presence of sleep problems.

f. Between-group comparisons of improvements in sleep beliefs and attitudes (DBAS-16) before and after intervention in the two groups of patients;

Dysfunctional beliefs and attitudes about sleep (DBAS) (43) is primarily used for cognitive situations related to the evaluation of sleep and is a self-assessment tool for misconceptions about sleep. Morin et al. proposed a simplified 16-item (DBAS -16) version of the original 30-item scale in order to simplify its administration and increase the usefulness of the scale. Subjects rate the ideas in the scale on a visual scale. Eleven numbers from 0 to 10 are marked on a 100 mm long line. 0 means strongly disagree and 10 means strongly agree.

g.The number of remitters and responders of study group.

Applicability Indicators: a. All-cause shedding rate;

b. Patient experience based on semi-structured qualitative interviews. The interview outline centered on the patient’s experience of using Smart CBT-I plus treatment, such as: how do you feel about Smart CBT-I plus, how was the experience during the use, what impressed you or what was the most impressive content or fragment in the use, etc. This interview will be terminated when the patient has no new expression related to his experience;

c. Patient completion rates with Smart CBT-I plus;

d. Average usage time of the application.

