### Trial design

2.1

This will be a single-center, parallel group, randomized controlled trial. A total of 180 patients with insomnia disorder combined with anxiety and/or depressive symptoms will be recruited and randomly assigned in a ratio of 1:2 to the online psychoeducation group (control group) and the Smart CBT-I plus treatment group (study group), and followed up at 6 months, and 12 months after the treatment. Both the control and study groups will be done online.

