### Participants and eligibility

2.3

Participants will be included in this study if(1)Considering that minors under the age of 18 do not have a strong sense of rights and interests to participate in the study, and elderly people over 65 have difficulty in using electronic devices, the inclusion criteria for this study is 18-65 years old age; (2)Currently meets DSM-5 diagnostic criteria for insomnia disorder; (3)Insomnia Severity Index(ISI)total score ≥15; (4)Concomitant anxiety and/or depressive symptoms, 14 points ≤ HAMA ≤ 29, 14 points ≤ HAMD-17 ≤ 23; (5) Adequate literacy and understanding to complete the required inspections and assessments for this study;(6)No sedative, antidepressant, anxiolytic, or antipsychotic medication was taken 2 weeks prior to enrolment, or the type and dose of the medication was stable for 4 weeks prior to enrolment. The type and dose of the drug is stable; (7)they volunteered to participate and signed the ICFs after fully understanding all aspects of the trial.

Participants will be excluded from the study if they meet the following criteria.(1)Other sleep disorders that meet DSM-5 diagnostic criteria, such as apnea syndrome, restless legs syndrome, etc.; (2) female who are pregnant, breastfeeding, or planning to become pregnant during the study period; (3) insomnia problems caused by alcohol or substance abuse; (4) severe cognitive problems; (5) patients with a previous or current diagnosis of bipolar and related disorders, obsessive-compulsive and related disorders, schizophrenia spectrum and other psychotic disorders, trauma and stress-related disorders, dissociative disorders, eating disorders, etc.; (6) patients with significant negative suicidal risk and a HAMD-17 item 2 score of ≥2; (7) patients with a history of epilepsy or other serious physical illnesses; (8) those who have been treated with MECT in the last month; (9) those who have received systematic psychological treatment for more than 3 consecutive months but found it to be ineffective; (10) those who are unable to tolerate the study setting; and (11) those who, in the opinion of the investigator, are unsuitable for the other conditions to participate in this study. For example, the researcher felt that the patient could not guarantee full and complete participation in the study, or that the patient would have a life change such as pregnancy plan that would not be suitable for inclusion in the study.

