## Statistical analysis

4

The datasets included in the statistical analyses will be divided into the Full analysis set (FAS) and the Per Protocol Set (PPS). FAS refers to people who have had at least one follow-up after enrollment and have data on key indicators. Cases missing baseline data for the primary evaluation indicator will be excluded. PPS refers to cases that meet the inclusion and exclusion criteria on the basis of FAS, have valid baseline values, have good adherence, and do not violate the clinical study protocol. Data will be analyzed using both the FAS and the PPS, with FAS results being the mainstay.

Statistical tests will be performed using SPSS version 23.0 software and relevant data will be considered statistically significant if P < 0.05. Comparisons between groups will be made using chi-square analysis, continuous variables will be statistically described using mean ± standard deviation (M ± SD), comparisons between the two groups will be made using the independent samples t-test, and repeated measures such as ANOVA will also be used to compare the degree of symptomatic improvement in the intervention group and the control group and to analyze the group × time interaction. In addition, Binary Logistics regression and COX regression will be used to compare the changes in each indicator before and after the intervention between the two groups. Multiple imputation will be used for handling missing data.

Data will be analyzed using content analysis to extract patients’ experiences of using the Smart CBT-I plus. The audio recordings of the semi-sectional constructed interviews will be transcribed into text before the interview data is independently coded and analyzed by each of the 2 researchers, and if inconsistencies are encountered, they will be discussed to reach consistent conclusions, and inter-researcher coding consistency will be used to rate the study’s reliability.

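### HAMA, HAMD and PSQI totals are compared as unadjusted reduction rates: a small loss of power if both HAMA and HAMD entry ranges bind, a larger one for HAMA and HAMD if either suffices

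*Protocol article*

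**What the plan says.** Section 3 of the protocol article lists, as secondary indicators, a "Between-group comparison of the total HAMA score reduction rate in the two groups of patients" and a "Between-group comparison of the HAMD total score reduction rate in the two groups of patients". For sleep quality it lists the "Pittsburgh Sleep Quality Index (PSQI) total score reduction rate and the change of each factor score". The term reduction rate is not defined. By contrast, the main indicator (ISI) is compared as scores, sleep latency and sleep duration as changes in time, and the PSQI factors as plain change.

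For continuous outcomes, Section 4 says that "comparisons between the two groups will be made using the independent samples t-test". It adds repeated-measures ANOVA with a group × time interaction, and names no analysis adjusted for baseline.

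On who enters, Section 2.1 says "A total of 180 patients with insomnia disorder combined with anxiety and/or depressive symptoms will be recruited". The criterion in Section 2.3 reads "Concomitant anxiety and/or depressive symptoms, 14 points ≤ HAMA ≤ 29, 14 points ≤ HAMD-17 ≤ 23", with nothing between the two ranges to say whether both or only one must be met. All patients must also have "Insomnia Severity Index(ISI)total score ≥15". No PSQI entry limit is given.

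**The concern.** A percentage fall divides by the patient's own baseline, so the same change in points counts for more when the baseline is low. The rate cannot exceed +100% but has no comparable lower limit. A patient who worsens from a low baseline therefore yields a large negative value that inflates the standard deviation. If entry requires anxiety or depression but not both, a patient who enters for depression may have a low HAMA, and the reverse.

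HAMA and HAMD are the clinician-rated measures of what the added anxiety and depression modules are meant to improve. At stake is the precision of those comparisons. Even without low baselines, an unadjusted percentage uses the baseline less efficiently than a model with baseline as covariate.

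**Working it through.** The article gives no power figure for these endpoints, so there is none to reproduce. The check has three steps.

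**1. Leverage of the baseline (arithmetic only).** Rate = (baseline − post) / baseline. A 3-point fall gives:
- baseline 29: 3/29 = 10%
- baseline 14: 3/14 = 21%
- baseline 7: 3/7 = 43%
- baseline 4: 3/4 = 75%

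A HAMA rising from 3 to 8 gives (3 − 8)/3 = −167%. Baselines below 14 can occur on HAMA or HAMD only if either entry range suffices.

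**2. Power, evenly spread baselines.** From the article: 60 control and 120 study patients, 15% dropout, two-sided 5% (the article does not state sidedness). Evaluable: 60 × 0.85 = 51 and 120 × 0.85 = 102. Assumed, not in the article: HAMA baseline uniform from a lowest value to 29; post = 2 + 0.65 × baseline − 2.5 (study group) + normal error with SD 5, rounded and floored at 0. The simulation was run twice; where the runs differ, both results are shown.

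| Lowest baseline | Share below 14 | t-test on rate | ANCOVA on score |
|---|---|---|---|
| 14 | 0% | 80–82% | 82% |
| 7 | 7/22 = 32% | 77–78% | 82–83% |
| 4 | 10/25 = 40% | 71% | 80–81% |
| 2 | 12/27 = 44% | 61% | 81% |

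The first row corresponds to both ranges binding, the others to either sufficing. With no true effect, the t-test on the rate rejected in 4.2% to 5.0% of 4,000 trials at every floor.

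**3. Power under other assumptions.** Same 51:102, true effect 0.5 SD of the post score (the effect size in Section 2.7), baseline–post correlation r of 0.3, 0.5 and 0.7. Assumed: HAMA baseline mean 19 (SD 4.5), post SD 6; HAMD 17.5 (3), 5; PSQI 13.5 (3), 3.5; control scores falling 25–30%. For the either-range reading, one third of patients are low on the scale. The effect is additive, and for HAMA also proportional to baseline.

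| Scenario | Loss, rate against ANCOVA |
|---|---|
| HAMA and HAMD, both ranges bind | about 0.5–4 points |
| HAMA and HAMD, one third at 7–13 | about 1–17 points |
| HAMA and HAMD, one third at 3–13 | about 4–40 points |
| PSQI, baselines 8–21 | about 1–4 points |

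Two examples for HAMA with an additive effect and r = 0.5: 0.878 against 0.889 if both ranges bind, and 0.738 against 0.915 with one third at 3–13. At r = 0.3 the control-arm SD of the HAMA rate is 30 percentage points with a floor of 14, 45 with one third at 7–13, and 72 with one third at 3–13. The rate had lower power than ANCOVA in every scenario.

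The planned group × time test, with two visits, is a comparison of change scores. In the second HAMA example its power is 0.756, also below ANCOVA at 0.915.

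**The case against.** The strongest objection is that low baselines may not occur. Section 2.3 is the operative criterion, and it lists the HAMA and HAMD-17 ranges one after the other with no word for or. If both bind, no baseline on either scale is below 14, the patient going from 3 to 8 could not enrol, and little is left of the loss. Section 1.2 also speaks of anxiety and depression together. Against this, the abstract's methods and Sections 2.1 and 2.2 all use and/or, and requiring both ranges would exclude the patients with only one set of symptoms whom those sections recruit. The text does not settle the matter, so the larger losses can be stated only conditionally.

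A reader might infer four further things that the document does not support:
- **That PSQI is unstable for the same reason.** The anxiety or depression rule does not bear on PSQI, and ISI of at least 15 makes low PSQI totals unlikely. Only the general loss of efficiency applies.
- **That the scores are discarded.** Repeated-measures ANOVA is planned as well, so the rate is not the only comparison. What is missing is adjustment for baseline.
- **That the comparison is biased.** Under randomisation, chance baseline imbalance costs precision, and the simulated type I error stays near 5%.
- **That the trial's main conclusion is affected.** Section 3 defines success by ISI scores after 35 days; HAMA, HAMD and PSQI are secondary.

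All four limits stand. They reduce the size of the point but do not remove it: the article itself fixes the rate as the endpoint, so this is not a detail left to a statistical analysis plan.

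**Conclusion.** The point holds as a loss of efficiency on secondary endpoints, of a size that depends on how Section 2.3 is read. If both ranges must be met, HAMA and HAMD lose about 0 to 4 points of power, and PSQI about 1 to 4 on either reading. If either range suffices, the HAMA and HAMD rates become skewed and unstable. The loss is then roughly 5 to 20 points with evenly spread baselines, and from about 1 to 40 across the wider set of assumptions. The article gives no baseline distribution, so these figures show direction and order of size and are not forecasts. They also rest on reading the undefined rate as percentage fall from baseline.

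**What to change.** In Section 3, replace the three reduction rates by the HAMA, HAMD and PSQI total scores. Compare them by ANCOVA at the post-intervention visit, or by a mixed model across the post-intervention, 6-month and 12-month visits, with the V1 score as covariate. Report the adjusted mean difference with its 95% CI, and name the time point, since Section 3 gives none for HAMA and HAMD. Keep percentage reduction as a descriptive figure only, and define it.

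Separately, reconcile Section 2.3 with the and/or wording elsewhere by stating whether both the HAMA and HAMD-17 ranges must be met or one is enough. The change of analysis does not depend on which it is.

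The cost is wording only. Table 1 already schedules all three scales at V1 and at every later visit, so no new data and no extra patients are needed.

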### Participant timeline

2.6

At baseline and at the end of the intervention, patients will be subjected to a series of psychological assessments, including sleep and mood symptoms. For patients in the study group, at the end of the 35-day intervention, a random sample of 30 patients will also be given a one-on-one qualitative interview to discuss their experience with Smart CBT-I plus, the interview results will be recorded. All patients will be evaluated at follow-up at 6 and 12 months after completion of treatment. Patients will be made aware of all assessment results. They will also be able to view their weekly assessments on their own in the program. they will still be able to use the program on their own after the 35-day session. The specific follow-up schedule is shown in **Table 1**.

**Table 1 T1:** Subject visit schedule.

items	Screening visit	Baseline visit	Post-intervention visit	Follow-up visit	
Visit	V0	V1	V2	V3	V4
Time	Day -7-0 * (± 1 day)	Day 0 (± 1 day)	35 days after baseline (± 3 days)	6 months after intervention (± 7 days)	12 months after intervention (± 7 days)
Sign informed consent	**×**				
Inclusion/exclusion criteria	**×**	**×**			
Self-made general demographic questionnaire		**×**			
Self-made clinical feature collection scale		**×**			
Semi-structured sleep assessment questionnaire		**×**			
Insomnia Severity Index Scale (ISI)	**×**	**×**	**×**	**×**	**×**
Hamilton Depression Scale (HAMD)	**×**	**×**	**×**	**×**	**×**
Hamilton Anxiety Scale (HAMA)	**×**	**×**	**×**	**×**	**×**
Clinical Gross Impression Scale (CGI)		**×**	**×**	**×**	**×**
Epworth Sleepiness Scale (ESS)		**×**	**×**	**×**	**×**
Pittsburgh Sleep Quality Index Scale (PSQI)		**×**	**×**	**×**	**×**
Hygiene economics evaluation		**×**	**×**	**×**	**×**
Adverse event report form			**×**	**×**	**×**
Serious Adverse Event (SAE) report form			**×**	**×**	**×**
Six quality of life questionnaires		**×**	**×**	**×**	**×**
Generalized Anxiety Scale (GAD-7)		**×**	**×**	**×**	**×**
Dysfunctional Beliefs and Attitudes about Sleep Scale (DBAS-16)		**×**	**×**	**×**	**×**
Rapid Report of Depressive Symptoms - Self-report score 16 items (QIDS-SR16)		**×**	**×**	**×**	**×**
Life Event Scale (LES)		**×**			
Therapeutic Alliance Questionnaire Revision (WAI-S)			** *×* **		
Outline of semi-structured qualitative interviews (30 patients of study group)			** *×* **		
medication administration record	**×**	**×**	**×**	**×**	**×**

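### Responders and remitters are counted in the study group only, and uncontrolled within-group ISI tests are listed as a main indicator said to confirm the effect

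*Protocol article*

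**What the plan says.** Protocol article, section 3 (Outcome measurements and instruments):

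- The main indicator has two parts: "Between-group comparison of ISI scores between the two groups after intervention and within-group comparisons before and after the intervention".
- Success is defined by the between-group part alone: after 35 days, "a significant difference in the ISI scores between groups is found in the study group compared to the control group".
- The within-group part is given a further role. These comparisons "will be explored thereby confirming the effect of the intervention more clearly".
- Secondary indicators a to f are all comparisons of the two groups, for example "Between-group comparison of the total HAMA score reduction rate in the two groups of patients". Indicator g is "The number of remitters and responders of study group", with no control count and no comparison.

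Elsewhere in the article:

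- Section 2.3 selects patients on "Insomnia Severity Index(ISI)total score ≥15".
- Table 1 (section 2.6) schedules ISI at screening (V0), baseline (V1), post-intervention (V2) and both follow-ups. It marks the eligibility criteria at both V0 and V1. The only row limited to one arm is the qualitative interview.
- Section 4 plans chi-square tests, t-tests, repeated-measures ANOVA with group × time, and logistic and Cox regression, comparing the two groups.

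**The concern.** A count of responders in one arm cannot separate the effect of the app from what would have happened anyway. The stated objective is a comparison with psychoeducation, and the control data will exist, so the restriction gives up controlled evidence that costs nothing to obtain.

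The within-group tests have the same weakness and a stronger claim attached. A fall in ISI from before to after has several possible sources in this design:

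- selection on a high ISI score;
- the natural course of insomnia;
- continued medication and the short-term sleep medication allowed in section 2.5.1;
- the one-hour therapist interview in section 2.2;
- psychoeducation, which section 2.5.2 itself expects to help.

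A significant pre-post test does not tell these apart from an effect of Smart CBT-I plus. The 1:2 allocation adds a trap: with the same fall in both arms, the larger arm reaches significance more often. If the plan is followed as written, two declared efficacy results could be reported as support for the app without resting on a comparison.

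**Working it through.** **No figure to reproduce.** The article gives no number on this point, and no ISI mean, SD or test-retest correlation. All ISI parameters below are assumptions. From section 2.7: 60 control and 120 study patients with 15% dropout leave 60 × 0.85 = 51 and 120 × 0.85 = 102 completers. Tests are two-sided at 0.05.

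**1. Regression to the mean alone (no treatment effect, no natural change).** The answer depends on which visit's ISI score does the selecting. Assume normal scores with source mean μ, SD 5 and correlation r between any two visits.

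*Cut-off applied at V0 only.* V1 and V2 are then both fresh measurements with the same expected value. The expected V1-to-V2 fall is 0, and each arm is significant in 5% of trials.

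*Cut-off applied at V1 only.* Expected fall = 5 × (1 − r) × λ, where λ = φ(a)/(1 − Φ(a)) and a = (15 − μ)/5.

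- μ = 15, r = 0.7: a = 0 and λ = 0.798, so the fall is 5 × 0.3 × 0.798 = 1.2 points.
- Variance of change = (1 − r)² × 25 × (1 − λ²) + 25 × (1 − r²) = 0.09 × 9.08 + 12.75 = 13.57, so the SD is 3.68.
- Standardised fall = 1.197/3.68 = 0.325. Noncentrality is 0.325 × √102 = 3.28 (study) and 0.325 × √51 = 2.32 (control).
- The noncentral t gives about 90% (study) and 62% (control).

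*Cut-off applied at both V0 and V1.* There is no simple formula. Simulation in the same setting gives a fall of 0.8 points, significant in about 59% (study) and 33% (control).

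| Assumed setting (SD 5) | Cut-off at | Study, n = 102 | Control, n = 51 |
|---|---|---|---|
| any mean and correlation | V0 only | 5% | 5% |
| mean 15, r = 0.7 | V0 and V1 | 59% | 33% |
| mean 15, r = 0.7 | V1 only | 90% | 62% |
| mean 19, r = 0.7 | V0 and V1 | 18% | 11% |
| mean 19, r = 0.7 | V1 only | 31% | 18% |
| mean 13, r = 0.6 | V1 only | over 99% | 95% |

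Over means 13 to 19 and correlations 0.6 to 0.8, the range is 5% to over 99% in the study arm and 5% to 95% in control.

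**2. All non-specific sources together.** Suppose both arms fall by 2 ISI points for reasons unrelated to the app, with SD of change 4 to 5 (assumed). The chance of significance is about Φ(2√n/SD − 1.96).

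- n = 51: SD 4 gives Φ(3.57 − 1.96) = 0.95; SD 5 gives Φ(2.86 − 1.96) = 0.82.
- n = 102: SD 4 gives Φ(5.05 − 1.96) = 0.999; SD 5 gives Φ(4.04 − 1.96) = 0.98.

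**3. Effect of unequal arms.** In the setting with 90% and 62%, the chance that only the study arm is significant is 0.90 × 0.38 = 0.34. The chance that only control is significant is 0.10 × 0.62 = 0.06. Nothing differs between the arms except their size.

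**4. What a two-arm version of g could detect.** Power = Φ((Δ − 1.96 × SE₀)/SE₁), with SE₀ from the pooled proportion and SE₁ from the separate ones. The rates are assumed, since the article gives none.

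- 20% control against 45% study: pooled proportion 0.367, SE₀ = 0.0826, SE₁ = 0.0746, so (0.25 − 0.162)/0.0746 = 1.18 and power is 0.88.
- By the same formula: 30% against 55%, 0.85; 20% against 40%, 0.71; 40% against 60%, 0.65.

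The planned numbers therefore support a useful comparison for differences of about 25 points or more.

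**The case against.** The strongest defence is that none of this decides the trial. Success rests on the between-group ISI difference, the within-group comparisons are described as exploratory, they are made in both arms so the control change is visible, and section 4 plans the group × time test, which is the right one. That stands, and it limits the severity.

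A second defence is that section 4 plans logistic regression comparing each indicator between the groups, so g may be a terse line in a condensed article. That stands only in part. Section 4 is general, while g names one arm explicitly and is the only secondary indicator to do so. The two sections conflict and need reconciling. Responder and remitter cut-offs may be in the full protocol, and their absence is not counted here.

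A reader might infer more than the article supports, in two ways:

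- *That regression to the mean alone would make the within-group tests significant.* Table 1 has separate screening and baseline ISI scores, and the article does not say at which visit the cut-off applies. If it applies at V0 only, the expected fall is zero. A clinic population with a higher source mean also shrinks it.
- *That the authors will take significance in one arm but not the other as proof.* The article states no such rule. It is a misreading that the wording invites, not one that it plans.

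**Conclusion.** The point holds as a correction that should be made, but not as a threat to the primary conclusion. Two things are fixed badly in the text itself: g is restricted to one arm, against the pattern of a to f and the methods in section 4; and an uncontrolled pre-post comparison is placed among the main indicators and said to confirm the effect.

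The part about g needs no assumption. The claim that pre-post tests cannot confirm an effect also needs none; only its size does. A non-specific fall of 2 points is an assumed figure, but at that size significance is close to certain in the study arm and likely in control. The share due to regression to the mean alone cannot be pinned down from the article.

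**What to change.** 1. Reword g as the proportions of responders and of remitters in each arm, compared between arms by a risk difference with 95% CI, or by logistic regression adjusted for baseline, in the plan's main analysis set (the FAS). Align section 4 with this.
2. Move the within-group ISI comparisons out of the main indicators. Report mean change with its CI in each arm as description.
3. Delete the statement that within-group comparisons confirm the effect. The between-group and group × time comparisons remain as the evidence of effect.

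Cost: no extra data, visits or patients, because Table 1 already collects the scales in both arms. The change is a few lines of text and one more column in a results table.
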